### Patient and public involvement

2.5

Neither the patients nor the public will be involved in the design, implementation, reporting or planning of this study at any stage of the research process.

### Sample size

2.6

The calculated sample size for this study is 90 patients: 45 patients in the experimental group and 45 patients in the control group. This is a randomized controlled study in which the experimental group will be treated with a TCM hot compress and the control group will be treated with a sea salt hot compress (a hot compress of a improved Xiao-Xu-Ming-Tang and salt mixture, making the two groups indistinct in smell) The primary outcomes will be the incidences of moderate and severe CRBD in patients with indwelling catheters after transurethral laser lithotripsy. According to previous studies, the incidence of moderate-to-severe CRBD after transurethral laser lithotripsy is 55–87% (3, 9, 20), with an average of approximately 70%. Assuming that the improved Xiao-Xu-Ming-Tang hot compress can reduce the incidence of CRBD by 50%, that is, the incidence of CRBD in the control group and the experimental group are 70 and 35%, respectively. Considering an *α* = 0.05 (two-tailed), a 1 − *β* = 0.9, and a 1:1 ratio, 42 patients are needed for the control group and 42 are needed for the experimental group. However, considering a loss to follow-up rate of 5%, approximately 45 patients will be included in each group.

### Data management and statistical analysis

2.7

All the statistical analyses will be performed with SPSS version 27.0 (IBM Corporation, Armonk, NY, United States). The baseline data will include clinical data collected before the first intervention. Normally distributed continuous variables will be expressed as means ± standard deviations (SDs); otherwise, they will be expressed as medians and interquartile ranges (IQRs). Categorical variables will be described as numbers (*n*) and percentages (%). The chi-square test will be used to compare the incidence between the two groups, the t test will be used to compare normally distributed continuous variables, and the nonparametric test will be used for other variables. All hypothesis tests are two-sided, and two-sided *p*-values less than 0.05 represent statistical significance.

TSA 0.9.5.10 beta software will employed to verify study power, with preset parameters including two-sided *α* = 0.05, *β* = 0.1, and an expected RRR of 50%. Using the primary outcome (incidence of moderate–severe CRBD), we will derive the cumulative *Z*-value and establish the monitoring boundary to guard against false positives and false negatives induced by multiple testing.

For NNT reporting, we calculate and report the NNT (95% CI) for the primary endpoint (30-min post-surgery moderate–severe CRBD) in the Results section. Defined as 1/ARR, the NNT directly quantifies the clinical impact of the optimized Xiao-Xu-Ming-Tang hot compress, representing the number of subjects needed to prevent one instance of moderate–severe CRBD.

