#### Primary outcomes

2.2.1

The primary outcomes will be the incidences of moderate and severe CRBD (grades 3 and 4) at 30 min after surgery.

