### Randomization and masking

2.4

An envelope lottery will be used to randomize patients into groups, and because the study will be conducted across 3 centers, stratified randomization is required, with 30 patients included from each center, 15 of whom will be assigned to the experimental group and the remaining 15 will be included in the control group. The study will be conducted in double-blinded manner, and patients were only informed that they were enrolled in a clinical trial for the prevention of postoperative CRBD and were assigned to a study group with a unique study number, and the specific grouping (experimental/control) and the differences in the composition of the hot compress bags (full dose/one-tenth dose of medicinal powder) were not disclosed to the patients at any stage before, during, or after the surgery. The hot compress will be placed over the patient’s pubic symphysis immediately after intubation under general anesthesia and removed 60 min after surgery by a site nurse who will not be involved in follow-up visits. Patients, anesthesiologists, surgeons, note-takers, data registrars and analysts will be unaware of the group assignments. The TCM package will be distributed to each center by the Department of TCM of Shanghai Fourth People’s Hospital. Both groups will emit the smell of TCM, which are indistinguishable by odor alone. Group assignments will be maintained by the personnel at the main site who are not involved in the study but rather responsible for the study group numbers and hot compresses. Only when the patient has a serious adverse reaction that is suspected to be related to the intervention itself will he or she be responsible for the emergency unblinding of the patient to ensure timely treatment of the condition.

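### Randomisation is stratified by centre with a fixed 15/15 split, but the named primary test is an unstratified chi-square, whose type I error drifts below nominal when centres differ materially

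*Protocol article*

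**What the plan says.** Section 2.4 (Randomization and masking) makes centre a design factor: "stratified randomization is required, with 30 patients included from each center, 15 of whom will be assigned to the experimental group". The other 15 at each centre form the control group.

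Section 2.2.1 defines a binary primary outcome: "The primary outcomes will be the incidences of moderate and severe CRBD (grades 3 and 4) at 30 min after surgery". Section 2.7 (Data management and statistical analysis) names its test: "The chi-square test will be used to compare the incidence between the two groups". Continuous outcomes get a t test or a nonparametric test, and the number needed to treat (NNT) is promised with a 95% confidence interval. Centre appears nowhere in section 2.7.

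Section 2.6 (Sample size) is also an unstratified two-proportion calculation. It assumes that "the incidence of CRBD in the control group and the experimental group are 70 and 35%, respectively", and arrives at 42 per arm before loss.

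**The concern.** With equal arms in every centre, a difference in CRBD rate between centres cancels out of the treatment contrast. The pooled chi-square does not use this. Its variance comes from the overall event proportion, which includes the spread between centres. If that spread is material, the standard error is too large, the p-value tends to be too high, and the true type I error sits below 5% by an amount that depends on unknown centre rates. An interval for the NNT built on the crude risk difference, and the t tests on secondary outcomes, ignore centre in the same way.

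At stake are agreement between design and analysis, and a primary p-value whose operating level does not move with centre rates. The outcome is subjective and is graded by local evaluators, so centre differences are possible. The article gives no centre-specific rates.

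**Working it through.** **1. The plan's own sample size.** Inputs from section 2.6: 70% and 35%, two-sided α = 0.05, power 0.90, ratio 1:1.

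n = [1.960·√(2 × 0.525 × 0.475) + 1.282·√(0.70 × 0.30 + 0.35 × 0.65)]² / 0.35² = (1.384 + 0.848)² / 0.1225 = 40.7, so 41 per arm. The stated 42 is within one patient of this. For loss: 42 / 0.95 = 44.2, so 45, as stated. The sample size reproduces and is not at issue.

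**2. Why the pooled variance is too large.** The centre rates are assumed: 55/70/87%, the ends and approximate middle of the range that section 2.6 cites across previous studies. Under the null, with 45 per arm:

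- Mean rate = (0.55 + 0.70 + 0.87)/3 = 0.707.
- Pooled variance = 2 × 0.707 × 0.293 / 45 = 0.0092.
- Within-centre variance = 2 × [(0.2475 + 0.2100 + 0.1131)/3] / 45 = 2 × 0.1902 / 45 = 0.0085.
- Unrounded, the ratio is 0.009213 / 0.008453 = 1.090, so the pooled standard error is √1.090 = 1.044 times the correct one.
- The large-sample type I error is 2 × [1 − Φ(1.960 × 1.044)], about 4.1%.

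**3. Exact comparison.** All outcomes of three 2×2 tables were enumerated. The pooled Pearson test is d²/[p̄(1 − p̄)·2/n], where d is the crude risk difference, p̄ the overall event proportion and n the number per arm. CMH, without continuity correction, is the squared sum over centres of observed minus expected events, divided by the summed hypergeometric variances. Two alternatives were used: a risk ratio (RR) of 0.5 in each centre, as in section 2.6, and a common odds ratio (OR) of (0.35/0.65)/(0.70/0.30) = 0.231. Each cell gives chi-square / CMH, in %.

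| Per arm per centre | Control rates, % | Type I error | Power, RR 0.5 | Power, common OR |
|---|---|---|---|---|
| 15 | 70/70/70 | 5.35 / 5.02 | 92.0 / 92.0 | 92.0 / 92.0 |
| 15 | 65/70/75 | 5.25 / 5.01 | 92.0 / 92.1 | 91.6 / 91.8 |
| 15 | 60/70/80 | 4.97 / 4.98 | 92.2 / 92.5 | 90.3 / 91.1 |
| 15 | 55/70/87 | 4.37 / 4.92 | 93.0 / 93.9 | 86.6 / 89.6 |
| 14 | 70/70/70 | 5.06 / 4.90 | 92.4 / 90.5 | 92.4 / 90.5 |
| 14 | 65/70/75 | 4.97 / 4.89 | 92.5 / 90.7 | 92.1 / 90.5 |
| 14 | 60/70/80 | 4.69 / 4.88 | 92.6 / 91.4 | 90.9 / 90.1 |
| 14 | 55/70/87 | 4.11 / 4.92 | 93.4 / 93.0 | 87.3 / 87.6 |

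The rows with 14 correspond to the 42 evaluable per arm that section 2.6 plans for (3 × 14 = 42).

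**4. Reading.** In this table the type I error of CMH stays between 4.88% and 5.02%, while that of the chi-square runs from 4.11% to 5.35%. With 15 per arm per centre, CMH gains 0 to 0.9 points of power under RR 0.5 and up to 3 points under a common odds ratio. With 14, CMH is behind by 0.4 to 1.9 points under RR 0.5. Under a common odds ratio it ranges from 1.9 points behind to 0.2 to 0.3 ahead.

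**5. The estimate.** With 15/15 in every centre, each Mantel-Haenszel weight is 15 × 15/30 = 7.5. The weights are equal, so with complete data the stratified risk difference equals the crude one. Only the variance, the interval and the p-value change.

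**The case against.** Several points on the other side stand.

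- A reader might infer that the chi-square is conservative and loses power whenever centres differ. The calculations do not bear this out: at 65/70/75% with 15 per arm per centre its type I error is 5.25%, and power differs by 0.1 to 0.2 points.
- A reader might infer that centre differences of this size are expected. The article says only that "the incidence of moderate-to-severe CRBD after transurethral laser lithotripsy is 55–87"%, and that range is across earlier studies, not these three hospitals. Narrow eligibility, one catheter size, standardised anaesthesia and central evaluator training all limit heterogeneity.
- The 3-point power loss needs a common odds ratio. The plan specifies a 50% relative reduction, under which either test stays above 90% in every row.
- Section 2.6 allows for attrition ("considering a loss to follow-up rate of 5%, approximately 45 patients will be included in each group"). At the resulting 42 evaluable, the power advantage mostly disappears or reverses, so it is not right to say that power is simply being thrown away.
- Validity is not threatened. The crude difference is unbiased with equal arms in each centre, and the drift caused by centre differences is downward.

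The steadiness of CMH is not perfect either. With a common rate of 52.5% in all centres and 15 per arm, a simulation put both tests near 4.6%.

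The remaining argument is that centre adjustment belongs in an analysis plan that is not shown. That would answer a silence. Here section 2.7 names a test, and the test as named ignores the factor that section 2.4 requires. A separate plan may resolve this, but the article as written states a mismatch.

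**Conclusion.** The mismatch between sections 2.4 and 2.7 is real, and its consequence is modest. Under an assumed 55/70/87% spread with 15 per arm per centre, type I error is 4.4% against 4.9%, and power is 86.6% against 89.6% (common odds ratio) or 93.0% against 93.9% (RR 0.5). With mild or no centre differences and 15 per arm per centre, the tests are nearly equivalent. With 14, discreteness can put CMH behind by up to about 2 points.

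The reasons to change are that the analysis should follow the randomisation, and that CMH holds its level more steadily over the patterns examined. A promise of more power is not among them. Nothing here supports a reading that the trial is underpowered, that its estimate is biased, or that false positives are materially inflated. The figures rest on hypothetical centre rates, equal numbers evaluable in each arm and centre, and both tests run without continuity correction.

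**What to change.** In section 2.7:

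- Make the primary test a Cochran-Mantel-Haenszel test stratified by centre, and state that no continuity correction is applied.
- Report the Mantel-Haenszel risk difference with its 95% confidence interval, and derive the NNT and its interval from it.
- Include centre as a factor in the comparisons of continuous outcomes.
- Keep the crude chi-square as a sensitivity analysis.

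This costs a sentence or two, and the sample size is unchanged. It should be fixed before unblinding, so that no choice between crude and stratified p-values is left open. If a separate analysis plan already specifies a stratified test, section 2.7 should be brought into line with it.

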#### Secondary outcomes

2.2.2

The five secondary outcomes are as follows: (1) the incidence of moderate-to-severe CRBD at 1 h, 6 h, and 24 h after surgery; (2) the NRS score, which is used to evaluate postoperative pain, at 30 min, 1 h, 6 h, and 24 h after surgery, with scores ranging from 0, indicating no pain, to 10, indicating the worst pain imaginable; (3) the incidence of skin discomfort above the pubic symphysis (scald, redness, pruritus, allergy, etc.); (4) vital signs (blood pressure, heart rate, and oxygen saturation) at 10, 20, 30, 40, 50 min, 1 h, 6 h, and 24 h after surgery; and (5) patient satisfaction [24 h after surgery, patient satisfaction using a 5-point scale, with items graded 1 (“very dissatisfied”) to 5 (“very satisfied”)].

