#### Follow-up period: end of surgery to 24 h after surgery

2.8.3

NRS and RASS scores will be evaluated by a dedicated follow-up researcher at 30 min, 1 h, 6 h, and 24 h after surgery. CRBD grades and patient satisfaction scores will be recorded at the same postoperative time points. The researcher responsible for documentation will complete the CRF. Patients’ vital signs on admission to the PACU, intraoperative anesthetic agents, RASS, NRS, CRBD, and adverse events will be recorded in the electronic data system. The study timeline is presented in Table 1.

**Table 1 tab1:** Timetable of the study period.

Timepoint	Screening period (−2~−1 d)	Preparation period (−1~0 d)	Surgery period (0 d)	Follow-up period (after awakening until 24 h postoperatively)								
		T0		T1	T2	T3	T4	T5	T6	T7	T8	T9
Eligibility screen and informed consent	X											
General condition of the patient^a^	X											
Training^b^		X										
Vital signs^c^	X			X	X	X	X	X		X	X	X
Random allocation		X										
Hot compress												
The CRBD score						X				X	X	X
The NRS score						X				X	X	X
Adverse events record^d^												
Satisfaction of patients												

*T0, Before induction of anesthesia; T1, 10 min after awakening; T2, 20 min after awakening; T3, 30 min after awakening; T4, 40 min after awakening; T5, 50 min after awakening; T6, 1 h after awakening; T7, 6 h after awakening; T8, 12 h after awakening; T9, 24 h after awakening.

a Patients were educated about how to recognize CRBD (for example, suprapubic discomfort or burning with the urge to urinate) and how to distinguish them from surgical pain.

b Obtain the patient’s name, hospitalization number, age, medical history (whether there are the following conditions, serious heart, liver, kidney and other diseases; If the hot compress site has skin injury, ulcer, sensory disturbance, acute closed injury, suppurative infection or acute inflammation and other infectious diseases, skin diseases, severe diabetes, high fever and excessive use of product materials, it is not suitable for hot compress; Patients with prostatic hypertrophy, urethral stricture, and a history of indwelling catheter within 1 year.

c Blood pressure, heart rate, and oxygen saturation.

d Burns, redness, itching, allergies, etc.

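### Postoperative vital signs are, on the natural reading of section 2.7, compared without the screening value already collected: a valid test, but possibly less precise than it could be

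*Protocol article*

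**What the plan says.** Section 2.2.2 lists as its fourth secondary outcome "vital signs (blood pressure, heart rate, and oxygen saturation) at 10, 20, 30, 40, 50 min, 1 h, 6 h, and 24 h after surgery", which is eight postoperative times.

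Section 2.7 states the analysis for all continuous variables together: "the t test will be used to compare normally distributed continuous variables", and "the nonparametric test will be used for other variables". The significance rule is that "two-sided *p*-values less than 0.05 represent statistical significance". The only statement about baseline is a definition: "The baseline data will include clinical data collected before the first intervention". Baseline data are given no part in any comparison.

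Table 1 (section 2.8.3) has a row beginning "Vital signs^c^ X", and that first mark falls in the column headed "Screening period (−2~−1 d"). Random allocation is marked in the next column, the preparation period. A blood pressure, heart rate and oxygen saturation reading is therefore scheduled for each patient before allocation and before the compress.

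**The concern.** Patients differ in resting blood pressure and heart rate. In an unadjusted two-group comparison those differences stay in the error term. If the screening value predicts the postoperative value, conditioning on it removes part of that error at the price of one degree of freedom and no new data.

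The outcome has some weight for safety. The Introduction claims that the compress acts locally without systemic effects, while describing alkaloid constituents, ephedrine among them, that cross the skin well. Vital signs are the objective physiological measurement among the listed outcomes that bears on that claim. If no difference is found, the width of the interval decides how much reassurance the result gives.

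**Working it through.** **The plan's own figure.** The document states no precision target for vital signs. Its only sample-size figure concerns the binary primary outcome (section 2.6): 70% against 35%, two-sided alpha 0.05, power 0.90. With the pooled formula and mean proportion 0.525:

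n = [1.96·√(2·0.525·0.475) + 1.2816·√(0.70·0.30 + 0.35·0.65)]² / 0.35² = (1.384 + 0.848)² / 0.1225 = 40.7, so 41 per arm.

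The plan states 42, which agrees closely, and 42/0.95 = 44.2 rounds up to its 45. The sample size reproduces and is not affected by this point.

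**Inputs for the vital signs.**
- n = 45 per arm, N = 90 (section 2.6).
- Two-sided alpha 0.05 (section 2.7).
- Correlation r between the screening value and a postoperative value: not in the documents, so a range is assumed.

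**Formula.** At one time point, the variance of the baseline-adjusted difference relative to the unadjusted difference is

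(1 − r²) × (N − 3)/(N − 4) = (1 − r²) × 87/86.

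The second factor (1.012) is the price of estimating the slope and allowing for chance imbalance at baseline. The interval width scales with the square root of the ratio, and the equivalent unadjusted sample size is 45 divided by it. Without adjustment, the difference detectable with 90% power is (1.96 + 1.2816)·√(2/45) = 0.68 SD; with adjustment this is multiplied by the square root of the ratio.

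| Assumed r | 1 − r² | Variance ratio | Interval width ratio | Equivalent n per arm | Detectable difference (SD) |
|---|---|---|---|---|---|
| 0 | 1.00 | 1.01 | 1.01 | 44 to 45 | 0.69 |
| 0.2 | 0.96 | 0.97 | 0.99 | 46 | 0.67 |
| 0.3 | 0.91 | 0.92 | 0.96 | 49 | 0.66 |
| 0.5 | 0.75 | 0.76 | 0.87 | 59 | 0.60 |
| 0.7 | 0.51 | 0.52 | 0.72 | 87 | 0.49 |

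For an assumed true difference of 0.5 SD, power is 0.66 unadjusted, against 0.67, 0.70, 0.78 and 0.91 for r of 0.2, 0.3, 0.5 and 0.7.

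**Break-even.** The ratio equals 1 when r² = 1 − 86/87 = 1/87, that is r ≈ 0.11. Below that, adjustment costs at most about 1.2% in variance.

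**Schedule check.** Section 2.2.2 and Table 1 each give eight postoperative vital-sign times, but not the same eight. Section 2.2.2 includes 1 h, has no 12 h, and counts from surgery. Table 1 as extracted leaves 1 h blank, marks 12 h, and counts from awakening. Several other rows of the table are empty as extracted, so the layout may be damaged; the change of time origin stands in the table's footnote and does not depend on the layout.

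**The case against.** The strongest reply is that nothing here is wrong. Randomisation makes the unadjusted comparison valid, and chance baseline imbalance is already reflected in its standard error. That stands: a reader might infer that leaving out baseline biases the result, and it does not.

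Second, this is a condensed article, and covariates for a secondary outcome are often left to the analysis plan. That stands in part. Section 2.7 is not silent, however: it names a two-group test, and the point is about that choice. It does not rule out further modelling, so the unadjusted analysis is the natural reading and not an explicit statement.

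Third, a reader might infer that the plan commits to a separate test at every time and so to a long list of tests with false positives to expect. The text never says the comparison is made time by time. A t test takes one value per patient, which makes that reading likely, but it remains an inference. Nor would multiplicity support the change proposed here, because a mixed model that reports a difference at each time still contains the same comparisons.

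Fourth, the gain may be small. The screening reading is taken one to two days before surgery, and the outcomes follow anaesthesia and an operation, so r may be low; at r = 0.2 adjustment is worth about one patient per arm. Oxygen saturation sits near its ceiling and should gain little. This also stands, and a reader should not infer from the table that a large loss has been shown.

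**Conclusion.** The point holds as an optional improvement in precision. Section 2.7 fixes a two-group test with no role for baseline, while Table 1 schedules a pre-randomisation value for each patient.

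The benefit runs from about 3% lower variance at r = 0.2 to about 48% lower at r = 0.7, against a cost of about 1% at r = 0. These figures assume 45 evaluable patients per arm, a roughly linear relation between screening and postoperative values, and a correlation that the documents do not supply. The direction is secure for any r above about 0.11; the size is not known. The documents support no claim of bias or of an inflated error rate on this ground, and the primary outcome is unaffected.

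**What to change.** First reconcile the vital-sign schedule in section 2.2.2 with Table 1: whether 1 h or 12 h is measured, and whether time runs from surgery or from awakening. Arm-by-time terms cannot be fixed until this is settled.

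Then add to section 2.7, for systolic pressure, diastolic pressure and heart rate, one linear mixed model per sign:
- fixed effects for arm, categorical time, arm-by-time and centre, with the screening value as covariate;
- an unstructured covariance across times, or another structure named in advance;
- adjusted mean differences with 95% confidence intervals at each time, treated as descriptive, because the model does not itself control multiplicity.

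Naming the model in advance also stops an observed normality check from choosing the method for these signs. Oxygen saturation can stay with a simple comparison.

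The cost is a few sentences in section 2.7: no new data, no more patients, and the stated software fits the model. Section 2.1 gives a study period ending in November 2025, so the change should be fixed before unblinding or else be labelled as added later.
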